### Intervention

The intervention is described in Figure 1 as recommended by Perera et al [26]. The intervention includes the use of the TeNDER system, a tool created by the consortium of the TeNDER group under the coordination of the Visual Telecommunications Applications Group (Grupo de Aplicación de Telecomunicaciones Visuales; GATV) of the Polytechnic University of Madrid.

The TeNDER system integrates multiple monitoring sensors that provide data to build an integrated technological ecosystem. The patient is monitored on a daily basis through one or more devices that offer different monitoring records (Table 1). The type of device will be chosen by the participant unit according to the patient’s health status and their needs as expressed by the patient and their caregiver.

With the registered information, the TeNDER system will generate different functionalities (Textbox 1) that can be used through a mobile app and a web app. The functionalities for each participant will be activated according to their profile. Patients will have access to all functionalities, while caregivers and professionals will only be able to access functionalities that the patient authorizes.

Each participant unit will receive assistance in downloading and installing the app, creating an account, and creating a user profile. The use of the TeNDER system does not require advanced knowledge, only a basic user level. However, technical support will be provided by the GATV of the Polytechnic University of Madrid.

**Figure 1 figure1:**
[figure not shown]
Details of patient flow, the intervention, and data collection.

**Table 1 table1:** Devices and monitoring record.

Devices	Sleep quality detection	Emotional state detection	Physical activity^a^	Fall detection	Skeleton motion data^b^	Safety and security at home^c^
App for smartphones and tablets	✓	✓	✓	✓	✓	✓
Smartphone/tablet	✓	✓	✓	✓	✓	✓
Mini PC (low-end)	✓		✓	✓		
Mini PC (high-end)		✓			✓	✓
Speaker						
Smartband Fitbit			✓	✓	✓	✓
Environmental sensors (temperature and humidity)						✓
Microphone		✓				
Withings sleep analyzer (Withings France SA)	✓					
Localization sensor						✓
Open-close window and door sensors						✓
RGB camera (Intel RealSense)				✓	✓	

^a^Steps and heart rate.

^b^Balance, freezing, or both.

^c^Environmental status, door and window status, location, and activity at home.

Functionalities of the TeNDER system.
**Functionalities**
Monitoring of variables collected by devices and biosensorsConsultation of records and reports generated from the data collected by the biosensorsUse of a smart calendar in which to schedule important events, medical appointment reminders, and medication remindersPossibility to generate notifications, including reminders and alertsInstant messaging channel for the exchange of messages between patient, caregiver, and primary care health professionalRecommender function to explore a certain topic with the patient and, based on their answers, provide useful recommendations

### Data Collection

Two types of data will be collected based on the nature of the data: direct data (through questionnaires) and indirect data (through devices and biosensors).

#### Direct Data Collection

Once participants have agreed to participate in the study, they will be scheduled for the baseline visit (T0). At this visit, baseline and tool cocreation data will be collected. The final visit (T1) will take place 2 months after the intervention. Data collection during both visits will take place at the PCHC or at the patient’s home and will be carried out as face-to-face hetero-administered interviews by 2 project nurses. Data will be collected through questionnaires, and interviews will be indexed in an electronic data collection record (eDCR).

The primary outcome variable will be the QoL of patients measured using the SF36 questionnaire [23]. This is a 36-item questionnaire that includes 8 domains: physical functioning, role limitations due to physical problems, bodily pain, general health perceptions, mental health, role limitations due to emotional problems, social functioning, and vitality. Eight domain scores and a summary score (range 0-100) can be obtained; higher scores indicate better health-related QoL (HRQoL). In addition, six Likert-type questions are used to collect proxy indicators of QoL related to the TeNDER system. These questions are related to the perception of improved autonomy, support, improved self-care, and safety. In addition, we will collect sociodemographic variables such as sex, age, and nationality from patients, caregivers, and PCHPs. Also, technology affinity among the 3 types of users will be collected through a single ad hoc question. Clinical information collected from patients will include their main disease and other chronic diseases. The degree of autonomy and the need for help will be studied through ad hoc questionnaires at T0 and T1.

For a description of the usability of and satisfaction with TeNDER system after the intervention, the validated System Usability Scale questionnaire [24,25] will be administered to patients, caregivers, and PCHPs.

Caregivers’ QoL related to the care provided and the perceived satisfaction with the care provided will be studied through an ad hoc questionnaire.

The questionnaires (at T0 and T1) are included in Multimedia Appendix 1.

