### Objectives

The main objective of this study is to evaluate the effectiveness of a technological system (the TeNDER system) to improve QoL in patients with chronic diseases, including AD, PD, and CVD.

The secondary objectives are (1) to describe the satisfaction of patients, caregivers, and health professionals with the TeNDER system; (2) to describe the characteristics of the usability of the TeNDER system from the perspective of its potential users; and (3) to explore whether the use of the TeNDER system increases caregivers’ perceived satisfaction with the care provided and, in relation to this, improves their QoL.

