### Inclusion Criteria for Caregivers

Caregivers of the selected patients who are aware of the patient’s health and social situation and who provide direct care or support for daily activities will be included. In addition, caregivers must be able to use a smartphone.

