### Randomization

Once the participants have been selected, after the initial visit, the patients will be randomized by pathology. Patients included in the intervention group will be included together with their caregiver and PCHP, creating a participant unit (patient-caregiver-PCHP or patient-PCHP). There will be no masking in any phase of the study. Assignment will be performed centrally by the Research Support Unit of the Primary Care Management of Madrid.

Patients in the intervention group will be fitted with the TeNDER system device best suited to their needs and will be treated according to standard clinical practice. Patients in the control group will be treated according to standard clinical practice.

Subsequently, each PCHP will be informed of which patients have been assigned to each group; based on this, they will have a different role in each case (ie, using the TeNDER system with the intervention group and usual practice with the control group).

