### Storage and Security of Collected Data

All the direct data will be stored in an eDCR on the EUSurvey platform. This platform is developed by the Commission of the European Union and complies with the European Union Regulation No 2018/1725 of the European Parliament and of the Council of 23 October 2018, by which it guarantees data privacy through its policy on the protection of natural persons with regard to the processing of personal data. Only project researchers will have access to the data stored in EUSurvey by means of a username and password. The data collected will be pseudoanonymized using an alphanumeric code, and only the researcher administering the questionnaire to the participant will be able to link these data to the participant. The data stored will remain in the database for up to 25 years after the end of data collection in accordance with current regulations.

As for indirect data, the TeNDER System platform is hosted on domains recommended and endorsed by the European Union, which guarantees the highest standards of security and privacy protection. Once collected, the data are temporarily stored on the device itself for a few days if there is no connection to the TeNDER system. After connection, the data are stored in an anonymized form in the secure infrastructure of the TeNDER system and can be accessed by project researchers using credentials and tokens.

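### Ratings of TeNDER's usability and satisfaction are, as written, spoken face to face to project nurses with no control group; caregivers and professionals should complete them privately.

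*Protocol article*

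**What the plan says.** All references are to the Protocol article.

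- **Mode.** Direct Data Collection states one mode for the baseline and final visits: data collection "will be carried out as face-to-face hetero-administered interviews by 2 project nurses".
- **Instrument and respondents.** The same section uses a single instrument, once the intervention is over, to describe both how usable the system is and how satisfied its users are: "the validated System Usability Scale questionnaire [24,25] will be administered to patients, caregivers, and PCHPs". It gives no separate mode for this scale.
- **Purpose.** Under Objectives, the first secondary aim is "to describe the satisfaction of patients, caregivers, and health professionals with the TeNDER system". The second, on usability, is also descriptive.
- **Controls.** Randomization says: "Patients in the control group will be treated according to standard clinical practice". They do not receive the system.
- **Platform and respondents' abilities.** Storage and Security of Collected Data says: "All the direct data will be stored in an eDCR on the EUSurvey platform". It adds that whoever administers a questionnaire can link the answers to the respondent. Under Inclusion Criteria for Caregivers, "caregivers must be able to use a smartphone". The professionals are doctors and nurses.

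**The concern.** Respondents are asked to judge a system by staff of the project that provides it, aloud, and to someone who knows who they are. People tend to be kinder in that setting than on a private form.

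In a between-arm comparison, a shift of this kind may partly cancel. Here it cannot, because only users of the system can rate it and the result is a single-group description. Masking the interviewer would not help either, since the questions are about TeNDER itself. More respondents would only narrow the interval around the shifted value.

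At stake is the answer to secondary objectives 1 and 2. The Discussion covers lack of masking and the Hawthorne effect, for quality of life and adherence, and covers digital reluctance, for satisfaction and usability. It does not mention social desirability in the ratings.

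**Working it through.** **1. Does the interview mode cover these ratings?** The mode sentence in Direct Data Collection is general to both visits. The System Usability Scale is given after the intervention, which places it at the final visit, and no other mode is named. Study Population counts caregivers and professionals as participants alongside patients. The natural reading is that all three groups are interviewed. For professionals this is an inference, because the mode is not repeated for them.

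**2. Is there a comparison in which a shift could cancel?** No. Objectives 1 and 2 describe, and control patients have nothing to rate. Under Randomization, each professional uses TeNDER with the intervention patients and usual practice with the controls, so there is no separate control group of professionals.

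**3. How large could the effect be?** The plan gives no figure for this outcome. Its one power statement concerns SF36 and has no bearing here. The following is an illustration only.

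Inputs:
- Professionals: 187 × 0.45 = 84.15, so n = 84 (Recruitment).
- Intervention patients: n = 380 (Sample Size). That section gives 380 + 254 = 634 but states a total of 534. If the total and the 254 controls were right, n would be 534 − 254 = 280.
- Caregivers: no number is given.
- SD of the scale: assumed 15, 20 or 25.
- Constant upward shift b: assumed 2 or 4 points, the same for both groups.

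Formulas, with SE = SD/√n:
- half-width of the 95% confidence interval = 1.96 × SE
- coverage of the true mean = Φ(1.96 − b/SE) − Φ(−1.96 − b/SE)

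Example: n = 84, SD 20. SE = 20/√84 = 2.18 and the half-width is 4.28. For b = 4, b/SE = 1.83, and coverage is Φ(0.13) − Φ(−3.79) = 0.55.

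| Group | SD | Half-width | Coverage, b = 2 | Coverage, b = 4 |
|---|---|---|---|---|
| Professionals, n = 84 | 15 | 3.21 | 77% | 31% |
| | 20 | 4.28 | 85% | 55% |
| | 25 | 5.35 | 89% | 69% |
| Patients, n = 380 | 15 | 1.51 | 26% | 0.1% |
| | 20 | 2.01 | 50% | 3% |
| | 25 | 2.51 | 66% | 12% |

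With 280 patients and SD 20, the half-width is 2.34 and coverage is 61% (b = 2) or 8% (b = 4).

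The same shift does more harm to coverage in the larger group, because the interval is narrower. The bias itself is b in every row.

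**4. Is another mode feasible?** For caregivers and professionals, yes: one group must be able to use a smartphone and the other is clinical staff. For patients it is a trade-off. They are over 60, those with Alzheimer disease enter with a Mini Mental State Examination score of 19 to 28, and the Discussion expects some reluctance toward technology.

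**The case against.** - **The mode for caregivers and professionals is not spelled out.** The visits take place at the health center or the patient's home, which sounds like patient visits, and a journal article may leave mode by respondent to a fuller document. This stands as a caution. The text that is shown nevertheless sets one mode with no exception, so the point holds as written.
- **Interviewing is defensible.** It limits missing data and misunderstanding, and one mode keeps the three groups comparable. For patients this is persuasive, and the interview should stay. Splitting patient scores by mode would not isolate courtesy bias, because those who need help differ in cognition and digital skill.
- **The numbers are assumed.** This stands. A reader might infer from the table that the reported intervals will in fact miss the truth, or that upward bias is certain. The documents support neither: they give no shift and no SD, and the direction is only likely. Data Analysis and Statistical Plan ties confidence intervals to the quality-of-life difference; only the Abstract's general line on all analyses suggests one for these ratings.
- **EUSurvey may not allow self-entry.** A reader might infer that respondents could simply answer on the existing platform. The article describes it as the data record and limits access to stored data to researchers. Self-entry is neither mentioned nor excluded.
- **Self-completion can add its own bias.** Non-response may depend on satisfaction. This stands for a link sent out later, and much less for a form completed during the visit.
- **Problems can surface elsewhere**, through cocreation, user feedback and telephone support. It would therefore go too far to say that faults in the system will go unreported.

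**Conclusion.** The point holds in limited form. As written, uncontrolled descriptive ratings of the project's own system are collected by the project's own nurses in face-to-face interviews. Any social-desirability shift goes undiluted into the results for secondary objectives 1 and 2. Its direction is probably upward and its size is unknown; the coverage figures depend wholly on the assumed SD and shift, and the patient rows also on a sample size that does not add up.

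A reader might extend the criticism to the primary outcome. This point gives no ground for that, because SF36 is compared between arms and its procedure is not questioned here.

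The conclusion rests on reading the general mode sentence as applying to all three user groups. Priority: minor to moderate. Nothing in the plan is contradictory or miscalculated on this point, but a cheap improvement is available for two of the three groups.

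**What to change.** In Direct Data Collection, state that at the final visit caregivers and professionals complete the System Usability Scale and any TeNDER satisfaction items themselves, under their study code, without the nurse asking the questions or seeing the answers. Completion during the visit, on a tablet or paper form, is preferable because it limits non-response. A EUSurvey link is an alternative if the platform allows participant entry.

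Keep the nurse interview for patients. Report the results separately for patients, caregivers and professionals, with the mode stated for each. Add social desirability to the limitations for the patient ratings. Leave the SF36 procedure as it is.

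The cost is a form or tablet and a sealed or direct submission route, with somewhat less interview time. The downsides are possibly a few more unanswered items, and a mode that differs between patients and the other two groups, so differences in score between these groups should not be read as differences in opinion alone.

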#### Indirect Data Collection

Indirect data collection will be performed through devices and biosensors. These data are transmitted to the TeNDER cloud platform using an intermediary broker messaging service (RabbitMQ). A mini PC, on which the local health tracking tool server is installed, serves as a gateway for the biosensors to communicate with the cloud.

To ensure seamless data collection, most sensors are connected to the local area network wirelessly. The biosensors collect a wide range of data, including the following:

The Withings sleep analyzer captures sleep data, monitors heart rate and breathing rate, and is able to detect apnea states.The Smartwatch Fitbit Versa 2 detects heart rate and number of steps taken. In addition, raw accelerometer measurements extracted by the device help track fall incidents and patient location.A location sensor measures the signal strength of the smartwatch (via the Bluetooth connection) to determine position and presence at room level.A microphone and speaker provides real-time audio recording and is able to identify screams or cries through the collection of recordings and tone of voice.The Aqara Hub integrates several secondary devices, such as a room temperature and humidity sensor and binary door, window opening, and window closing sensors.The RealSense device captures the patient’s skeleton motion data in the form of coordinates in space. When combined with the Fitbit Versa 2 smartwatch, the system is able to identify the skeleton, and with the additional use of a microphone, can detect falls.

### Storage and Security of Collected Data

All the direct data will be stored in an eDCR on the EUSurvey platform. This platform is developed by the Commission of the European Union and complies with the European Union Regulation No 2018/1725 of the European Parliament and of the Council of 23 October 2018, by which it guarantees data privacy through its policy on the protection of natural persons with regard to the processing of personal data. Only project researchers will have access to the data stored in EUSurvey by means of a username and password. The data collected will be pseudoanonymized using an alphanumeric code, and only the researcher administering the questionnaire to the participant will be able to link these data to the participant. The data stored will remain in the database for up to 25 years after the end of data collection in accordance with current regulations.

As for indirect data, the TeNDER System platform is hosted on domains recommended and endorsed by the European Union, which guarantees the highest standards of security and privacy protection. Once collected, the data are temporarily stored on the device itself for a few days if there is no connection to the TeNDER system. After connection, the data are stored in an anonymized form in the secure infrastructure of the TeNDER system and can be accessed by project researchers using credentials and tokens.

### Data Analysis and Statistical Plan

A descriptive analysis of the characteristics of the participants will be performed with frequencies and percentages for qualitative variables and the mean (SD) or median (IQR) for the quantitative variables, according to their distribution. The mean difference in QoL score between the intervention and control groups will be studied with the corresponding 95% CIs at T1 (2 months). Differences in qualitative variables will be analyzed with the Pearson chi-squared test, and differences in normally distributed quantitative variables will be analyzed with the Student *t* test (2-tailed).

To study the effectiveness of the TeNDER System in improving QoL in patients, an explanatory linear regression model will be constructed. The dependent variable will be the mean difference in QoL score between the intervention and control groups at T1 (2 months). As patients will be recruited grouped by cluster (ie, PCHC), all the estimations will be performed with robust estimators. The analyses will be performed with Stata (version 14; StataCorp).

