## Discussion

Previous studies on the use of technological tools by people with chronic disease have shown an improvement in their self-management, self-care, and adherence to therapy. However, few studies have examined all users involved in the care of chronic patients in their use of these tools.

The strength of this work is to investigate the use of a technological tool focused on health and self-care by, on one hand, patients with chronic disease older than 65 years, and on the other hand, their caregivers or family supporters, as well as, finally, the health professionals who are responsible for monitoring their health status, in particular the PCHPs. This clinical trial among patients with highly prevalent chronic diseases and the people most involved in their care will provide a more realistic view of how technology can be integrated into their lives as an aid to care.

Another strong point is the involvement of users in the development and improvement of the TeNDER system. To this end, this work includes a cocreation phase in which the needs of the users are explored in order to develop a system that is adapted to them.

The main objective of this study is to improve the QoL of chronically ill patients older than 60 years. Despite the difficulties of achieving this with a 2-month intervention, there are certain proxy indicators of QoL that are sensitive to improvement, and this can be reflected in the HRQoL. Therefore, ad hoc questions have been included as variables that aim to detect elements that have an impact on QoL, such as safety and autonomy.

Among the main limitations are that due to the nature of the intervention, the trial cannot be masked. This may result in participants who are in the intervention group perceiving an improvement in their health follow-up; therefore, the difference in score with respect to the control group will increase. Thus, we propose to look for an increase of at least 6 points in the main improvement variable (QoL). In the same sense, the use of the TeNDER system can also lead to an improvement in patients’ adherence to treatment, as they feel observed and monitored by the system (ie, the Hawthorne effect).

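### The only test stated for categorical outcomes, Pearson chi-squared, ignores category order; if it is used for the six Likert-type proxy items, power against a one-directional shift is lost and no direction or size of effect is given

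*Protocol article*

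**What the plan says.** Under Direct Data Collection the primary outcome is fixed: "The primary outcome variable will be the QoL of patients measured using the SF36 questionnaire". The same section then adds the items at issue: "In addition, six Likert-type questions are used to collect proxy indicators of QoL related to the TeNDER system". They concern perceived autonomy, support, self-care and safety. No sum or scale score is described, and the number of response options is not given in the text.

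The Discussion explains why they are there. It concedes that improving quality of life with a 2-month intervention is difficult, then says that "there are certain proxy indicators of QoL that are sensitive to improvement, and this can be reflected in the HRQoL", and that "ad hoc questions have been included as variables that aim to detect elements that have an impact on QoL, such as safety and autonomy".

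Data Analysis and Statistical Plan gives two tests for group differences, chi-squared for categorical data and the t test for continuous data: "Differences in qualitative variables will be analyzed with the Pearson chi-squared test, and differences in normally distributed quantitative variables will be analyzed with the Student". Quantitative variables may be summarised by median and IQR when their distribution calls for it, but no test is named for that case. The linear regression is for the QoL score. All estimation is to use robust estimators because patients are grouped by health centre.

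**The concern.** A single Likert item has a few ordered answers. It is not a normally distributed quantity, so the t test branch does not fit it as worded, and the regression is reserved for the QoL score. Among the stated methods that leaves Pearson chi-squared.

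That test suits this kind of item poorly, for three reasons.

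- It gives the same p-value if the answer categories are shuffled, so it does not use the fact that one answer is better than another.
- It spreads a one-directional shift over k − 1 degrees of freedom.
- It yields no direction and no effect size. A significant result could come from answers moving to both extremes with no net improvement.

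The question asked of these items is directional: does perceived autonomy, support, self-care or safety improve? A real shift would be missed more often than necessary, and a positive result would still need a second analysis to say what it means.

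**Working it through.** **Inputs from the article.** Target difference 6 SF36 points; SD range 16 to 27, with 27 used for power; consortium arms 735 intervention and 1031 control; Madrid arms printed as 380 and 254. The Madrid total is printed as 534, but 380 + 254 = 634, so 380/154 and 280/254 were also run. Two-sided 5% is inferred from the 95% CIs and the 2-tailed t test.

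**Assumed, because the article does not give them.** Number of categories k = 3 to 7. Each item reflects a latent normal scale, with the intervention arm shifted by d. As a yardstick d = 6/27 = 0.222; with the smaller SD, d = 6/16 = 0.375. Clustering and dropout are ignored for both tests.

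**The plan's own figure.** The only power figure is 98.8% for SF36 in the consortium sample. z = 6 / (27 × √(1/735 + 1/1031)) = 4.60, and Φ(4.60 − 1.96) = 99.6%. This is within a point of the printed value. No power is stated for the Likert items.

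**Formulas.** Let p1j and p0j be the category probabilities, p̄j their sample-weighted mean and N = n1 + n0.

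- Pearson: λP = (n1·n0/N) Σ (p1j − p0j)²/p̄j, referred to chi-squared on k − 1 df.
- Ordered (rank) test: rj = Σ(i<j) p̄i + p̄j/2; λO = (n1·n0/N) [Σ rj(p1j − p0j)]² / [Σ rj²p̄j − (Σ rj p̄j)²], on 1 df.

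**Worked case: k = 5, equal control categories, d = 0.222, 380/254.** Control is 20% in each category. The shifted arm is 14.4, 17.3, 19.5, 22.0 and 26.8%. n1·n0/N = 96,520/634 = 152.2.

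- λP = 6.69; critical value 9.49 on 4 df; power 51.9%.
- λO = 6.62; critical value 3.84 on 1 df; power 73.0%.

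The two noncentralities are almost equal. Nearly all the signal lies in the order, and the three extra degrees of freedom cost about 21 points.

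**By number of categories (380/254, d = 0.222)**

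| k | Pearson | Ordered | Loss (points) |
|---|---|---|---|
| 3 | 57.8% | 68.2% | about 10 |
| 4 | 54.9% | 71.4% | 16.5 |
| 5 | 51.9% | 73.0% | 21.1 |
| 6 | 49.1% | 73.8% | 24.7 |
| 7 | 46.6% | 74.4% | 27.8 |

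A symmetric (10/20/40/20/10%) or skewed (5/10/20/35/30%) five-category distribution gives a loss of 20 to 21 points. Simulation with 20,000 replicates agrees: 55.3% v 71.3% (k = 4), 52.0% v 73.4% (k = 5) and 46.6% v 74.5% (k = 7), with type I error of 4.7 to 5.3% for both tests.

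**Other readings of the Madrid sample (d = 0.222, k = 4 to 7).** 380/154: loss about 16 to 26 points (k = 5: 38.4% v 58.8%). 280/254: about 17 to 28 points (k = 5: 45.9% v 67.2%).

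**Larger effects or sample**

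- d = 0.30, k = 4 to 7, all three readings: about 10 to 25 points.
- d = 0.375, k = 3 to 7, all three readings: about 2 to 14 points (380/254, k = 5: 95.2% v 99.1%).
- d = 0.50: under 2 points.
- Consortium sample 735/1031, d = 0.222, k = 4 to 7: about 3 to 6 points.

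**A check that needs no effect size.** If the ordered test has 80% power (λ = 7.85 on 1 df), the same noncentrality gives Pearson 70.9, 64.5, 59.5, 55.5 and 52.1% for k = 3 to 7.

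**The case against.** The strongest case against has four parts.

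First, the article never assigns the Likert items to chi-squared. They could be scored numerically and fall into the class of non-normal quantitative variables, for which no test is named, or they could be summed. They are described as related to the TeNDER system, so a between-arm comparison may not even be intended for all of them. This stands: the assignment is an inference and should be worded as one. It does not remove the point, because the chi-squared rule is stated for qualitative variables without exception, no score is mentioned, and the sponsor would need the same clarification under any of these readings.

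Second, an article condenses a fuller protocol, and the handling of supportive items is often settled elsewhere. That is fair for what is left unsaid. Here, however, a rule is stated, and as stated it is a poor fit for ordered answers.

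Third, a reader might infer that the trial depends on these items to show its effect. The documents do not support that. SF36 is the primary outcome, with its own mean difference, interval and regression. The proxy items appear in neither the Objectives nor the sample size, and the Discussion says only that they can respond and that this may be reflected in health-related QoL.

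Fourth, the 0.22 SD shift is borrowed from SF36 and uses the largest SD. If the items are more responsive than SF36, the true shift may be larger and the loss smaller. This also stands, and it is why the loss can only be given as a conditional range.

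**Conclusion.** The point holds in conditional form. As printed, the plan has no method for ordered categories, and its only categorical test discards order and gives no direction or size. If the six items are compared between arms with it, power against a one-directional shift falls by about 16 to 28 points, assuming 4 to 7 categories, a 0.22 SD shift and the Madrid sample under any of its three readings. With 3 categories the loss is about 10 points; at 0.375 SD it is 2 to 14 points; for large effects it is close to zero.

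It would be tempting to quote 16 to 28 points as a fixed cost of the plan. The documents do not allow that, because the number of categories and the effect on these items are not given. The lack of direction and effect size does not depend on those assumptions. The matter concerns supportive outcomes and leaves the SF36 analysis untouched.

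**What to change.** In Data Analysis and Statistical Plan, replace the chi-squared sentence with text along these lines:

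> Pearson chi-squared will be used for nominal variables only. Ordered items asked in both arms, including the six Likert-type proxy items, will be compared at T1 with a proportional-odds model, adjusted for the T0 response where the item is asked at T0. The common odds ratio will be reported with its 95% CI, using robust estimators clustered by health centre. A Wilcoxon rank-sum test will be a supportive check.

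Apply the same rule to ordered items in the ad hoc autonomy and need-for-help questionnaires. If the sponsor intends to sum the items, or to ask them in the intervention arm only, say so here.

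The model comes first because a standard rank-sum test takes no account of the grouping by centre for which the plan already requires robust estimation.

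The cost is a few lines of analysis text, with no new data, patients or staff. The small downside is that a common odds ratio assumes a similar shift across all category boundaries; the rank-sum check does not need that assumption to be valid.
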